### Measurements

Missing data will not be an issue, as the survey is conducted through LimeSurvey, where all questions are mandatory and cannot be skipped by participants.

To be included in the data analysis, participants must have completed all three measurement points and answered all questionnaires.

T1: First measurement: After the participant had signed the informed consent, the initial score for this outcome was assessed.T2: Second measurement: POST Up to 6 weeks after the second measurement, the second measurement of the same variable was carried out.T3: Third measurement: POST Up to 6 months after the second measurement, the third measurement of the same variable was carried out.

[Time Frame: Baseline up to 30 weeks]

Primary Outcome Measure:

Change Quality of Life (measured by KIDSCREEN-27).Change Emotional and Behavioral Problems (measured by SDQ).Change Emotional Competences (measured by EAQ-30).Change Self-concept (measured by CAG)Change Coping (measured by SPSI-R).Change Social Skills (measured by CHASO).

Secondary Outcome Measure:

Change Threat of disease (measured by BIP-Q)Change Psychoeducation Diabetes

Psychoeducation of the disease: the ECODI Diabetes knowledge scale will be used to assess this variable [79]. This scale consists of 25 items and four dimensions: basic knowledge and self-care, laboratory values, diet and physical exercise. It is a scale that is corrected by the number of hits and misses.

[Time Frame: Start of the game and during the game]

Change Resilience (measured by CD-RISC).

Other Pre-specified Outcome Measures:

Glycaemic control

HbA1c: It will be used to evaluate the glycemic control of the diabetic patient in endocrinology diseases.

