### Data analysis

In the present study, the per-protocol analysis (PP) approach was utilized to evaluate the effectiveness of the treatment and the management of missing data. This method includes only participants who fully adhered to the study protocol, ensuring that the results reflect the true efficacy of the intervention under ideal conditions. Participants will be included in the main analyses only if they have completed the treatment as per the protocol, that is to say, if they have adhered to all instructions without significant interruption. Participants who withdraw or fail to complete the treatment will be excluded from the analyses. This methodological decision is underpinned by the principle of minimizing potential bias from missing data, thereby ensuring that the results of the study accurately reflect the outcomes of participants who adhered to the treatment protocol. To address the issue of missing data during follow-up or treatment, predefined procedures will be implemented. The last observation carried forward (LOCF) imputation method will be employed to address missing data, with the last available measurement being utilised to complete the missing values. Furthermore, sensitivity analyses will be conducted to assess the impact of missing data on the study outcomes. These procedures are designed to minimise data loss, maintain the internal validity of the study, and ensure the robustness of the results.

Several statistical analyses will be performed to determine the effectiveness of *emoTICare*. As a first step, chi-square tests and t-tests were performed to examine potential differences between the control and experimental groups in key demographic and clinical variables (e.g., age, gender, disease duration). Although randomization is expected to ensure comparability, these tests were conducted to verify baseline equivalence. Propensity Score Matching (PSM) was not used to adjust for baseline differences, as the study followed a randomized controlled design.

Additionally, chi-square tests will compare the number of participants who withdraw from the experimental group with those who withdraw from the control group, ensuring no significant differences exist.

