Secondly, incidental sampling may hinder the generalization of the program’s results, as the sample may not fully represent the wider population of adolescents with Type 1 Diabetes. Thirdly, the online and remote format of the evaluation process, along with the use of the emoTICare program, may present challenges in ensuring proper completion, potentially increasing the likelihood of experimental mortality. Moreover, the online format could impact participant engagement, as the lack of direct interaction may lead to decreased attention or motivation. This is particularly relevant as maintaining participant motivation throughout the study period is a challenge in long-term interventions, and participants may experience fatigue or loss of interest over time. Additionally, biases in self-reported data could arise, as participants might provide socially desirable answers or misinterpret the questions, affecting the accuracy of the data. Conversely, per-protocol analysis (PP) provides a clear understanding of the potential benefits of treatment by focusing on subjects who have completed their assigned treatment regimen. However, it is limited in that it does not account for real-world challenges to adherence in real-world settings.

A further limitation of this study is the absence of specific data on the incidence of type 1 diabetes in individuals under 16 years of age. Instead, the incidence in individuals under 15 was used as a reference. It is acknowledged that this may result in under- or overestimation, owing to the exclusion of data from 15–16-year-olds. It is also noted that, given the relatively narrow additional age span (one year), any deviation in incidence is unlikely to significantly affect the overall power or feasibility estimates of the study. Incidence figures for individuals under 15 years are extensively utilised in international diabetes surveillance and are regarded as robust and comparable across populations. Given that the majority of the target population falls within the 12–14 age range, it was considered reasonable to use incidence data for individuals under 15 years as a proxy for estimating the expected number of eligible participants. Furthermore, the incidence of type 1 diabetes between ages 15 and 16 does not markedly deviate from that observed in the immediately preceding years, particularly in populations with relatively stable incidence curves.

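### The completer-only, per-protocol and LOCF rules cannot all operate, so the plan does not fix who is analysed; where LOCF does operate, it enters the T2 score as the six-month result

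*Protocol article*

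**What the plan says.** The protocol article deals with missing data in two places.

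**Measurements.** It opens by dismissing the problem: "Missing data will not be an issue, as the survey is conducted through LimeSurvey, where all questions are mandatory". It then sets an inclusion rule: "To be included in the data analysis, participants must have completed all three measurement points and answered all questionnaires".

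**Data analysis.** The approach is per-protocol: "Participants who withdraw or fail to complete the treatment will be excluded from the analyses". The same paragraph continues: "To address the issue of missing data during follow-up or treatment, predefined procedures will be implemented". The procedure it names is LOCF: "The last observation carried forward (LOCF) imputation method will be employed to address missing data, with the last available measurement being utilised". It also promises that "sensitivity analyses will be conducted to assess the impact of missing data on the study outcomes", without giving a method or an analysis set.

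Elsewhere the document expects losses. Sample size assumes 20% dropout. The Discussion says the remote format may present problems, "potentially increasing the likelihood of experimental mortality". Under Assessment tools, responses are invalidated when three or more infrequency items are answered wrongly.

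The six-month assessment is analysed. In Data analysis, the change from T1 to T3 is a dependent variable in the hierarchical regression, and a significant group term is to be attributed to the intervention.

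**The concern.** These rules decide who enters the analysis of all six primary outcomes. Two analysts could each follow the text, analyse different people and report different T3 effects. If the choice is left open, it could be made after the data are seen.

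The LOCF rule raises a second problem. T2 is taken immediately after the game and T3 six months later. Carrying T2 forward assumes that nothing changes in those six months, which is what the T3 minus T1 comparison is there to find out.

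**Working it through.** **1. Do the rules fit together?**

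- Three assessments required, and LOCF: everyone admitted has T1, T2 and T3, so LOCF imputes nobody. If LOCF imputes a missed assessment for anyone, the inclusion rule has been broken.
- Treatment non-completers excluded, and LOCF for data missing during treatment: someone who stops treatment is removed by one rule and imputed by the other.
- Treatment non-completers excluded, and LOCF for data missing during follow-up: these can coexist, but only for participants who finished treatment and then missed an assessment. If T3 is missing, T2 is entered. If T2 is missing too, T1 is carried forward and the change is set to zero.
- Mandatory items: these prevent skipped questions within a questionnaire that is submitted. They do not prevent a missed assessment, so the dismissal does not fit the 20% dropout and the attrition the document expects.

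**2. What LOCF does to the T3 effect.**

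Let m be the share of each arm missing T3 only (equal in both arms, missing at random), d2 the group difference at T2 and d3 the difference at T3, in SD units.

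Expected LOCF estimate = (1 − m) × d3 + m × d2, so bias = m × (d2 − d3).

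Inputs: 372 participants, equal allocation (186 per arm) and 20% dropout come from the document. The document calls the effect moderate without a number, so d2 = 0.5 is assumed. Setting m = 0.20 treats all dropout as missing T3 only, which is an upper case: 0.20 × 372 ≈ 74.

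| True d3 | LOCF estimate at m = 0.20 | Bias |
|---|---|---|
| 0.50 (fully retained) | 0.8 × 0.50 + 0.2 × 0.5 = 0.50 | 0 |
| 0.25 (half retained) | 0.8 × 0.25 + 0.2 × 0.5 = 0.30 | +0.05 |
| 0.20 | 0.8 × 0.20 + 0.2 × 0.5 = 0.26 | +0.06 |
| 0 (gone) | 0.8 × 0 + 0.2 × 0.5 = 0.10 | +0.10 |

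If the effect is gone at T3, the bias runs from 0.05 SD at 10% missing to 0.15 SD at 30% missing.

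**3. False-positive rate when the true T3 effect is zero.**

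The scenario was simulated with ANCOVA on T1, 186 per arm, an assumed correlation of 0.6 between assessments and 20% missing T3. LOCF gave an estimate of 0.10 SD and rejected in about 22% to 23% of runs at a nominal 5%. Analysing observed T3 scores only gave 0.00 SD and about 6%.

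A hand check agrees. The LOCF standard error is about 0.084, so 0.10 / 0.084 = 1.19 and 1.96 − 1.19 = 0.77. The upper-tail probability beyond 0.77 is about 0.22.

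**4. Unequal missingness.**

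Take an effect that fades from 0.5 to 0.4 SD, with both arms improving by 0.3 SD after T2. The arm means at T3 are then 0.7 (game) and 0.3 (control). Let 30% of the game arm and 10% of controls miss T3.

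LOCF estimate = (0.7 × 0.7 + 0.3 × 0.5) − (0.9 × 0.3 + 0.1 × 0) = 0.64 − 0.27 = 0.37.

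The true effect is 0.40, so here LOCF understates an effect that has faded.

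**The case against.** Five points can be made for the plan.

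*The analysis plan is not shown and the article is condensed.* Detail may well sit elsewhere, and the unnamed sensitivity analyses are not a fault in themselves. The objection, though, is to rules the article states and that exclude one another. A promised sensitivity analysis does not say which rule is primary.

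*Not every statement conflicts with every other.* This is right. The sentence on mandatory items concerns skipped questions and is compatible with a completer rule. It is over-optimistic, but the hard conflict is between completers only and LOCF.

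*LOCF may never be used, or may do no harm.* This is also right as far as it goes. If the completer rule governs, LOCF has no effect. If LOCF governs, the bias needs the group difference to change after T2, or missingness to differ between arms while scores trend over time. A reader might infer that LOCF overstates maintenance whenever the effect fades. Step 4 of the working shows that this fails.

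*The number affected is unknown.* A reader might take 74 of 372 as the expected number imputed. It is an upper case: those who withdraw or do not finish treatment would be excluded under Data analysis, and the document does not say how many would finish treatment and then miss T3.

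*LOCF does not necessarily understate the standard error.* A reader might expect that it does, since imputed values are treated as observed. In the simulated scenario the mean model standard error was 0.084 against an empirical SD of 0.082. The fault is that LOCF estimates the wrong quantity.

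**Conclusion.** The contradiction is in the text and needs no calculation: the three-assessment rule, the per-protocol exclusion and LOCF cannot all be applied, so the analysed population is not fixed. This should be settled before analysis.

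The bias is conditional. With equal missingness at random, LOCF shifts the T3 effect by m × (d2 − d3). Under the assumed 0.5 SD at T2 and 20% missing T3 only, that is +0.06 SD if the true T3 effect is 0.2. If it is zero, the shift is +0.10 SD with a false-positive rate of about 22%. The shift is nil if the effect persists and negative if it grows. With missingness that differs by arm and a time trend, it can go either way. The effect size, the share missing T3 only and the correlation of 0.6 are assumptions.

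A reader might also infer that a stated durability hypothesis is compromised. The document states no separate one: the hypotheses are framed around change from before to after the programme, and T3 enters as a change score in the regression.

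**What to change.** - Delete the sentence that dismisses missing data, the three-assessment inclusion rule and LOCF.
- State one primary analysis set: all randomised participants, with whatever data were observed. Move the per-protocol exclusion to a secondary analysis. If it stays in the primary analysis, the contradiction remains.
- Handle missing T2 and T3 scores by multiple imputation within arm, using T1 and earlier scores, age, gender and disease duration. This works inside the planned ANCOVA and regression models. A likelihood-based mixed model is an alternative, but the plan names none, so it would be an added model.
- Use the sensitivity analysis already promised to test departures from missing at random, for example by shifting imputed game-arm scores in the unfavourable direction until the conclusion changes.

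The cost is wording, standard software, some extra analysis work and somewhat wider confidence intervals than LOCF gives. As a guide, in the simulation the standard error was 0.093 for observed T3 scores only and 0.084 for LOCF. No new data are needed. The article says no stage had been completed and that data collection runs to February 2027, so on its own timeline the rule can be set in advance.

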### Sample size

In Spain, the report on “Prevalence of Diabetes Mellitus” [50] highlights that more than three million people in the country have diabetes, of which 3.4% have Type 1 Diabetes Mellitus (T1DM). The Spanish Diabetes Society [51] estimates that T1DM accounts for 1 in every 10 cases in Spain, totaling approximately 90,000 individuals with this condition. Specifically, the incidence of diabetes in individuals under 15 years old varies between 11 and 24 cases per 100,000 inhabitants per year [51].

To determine the sample size, we used a 95% confidence level and a 5% margin of error, which is a standard approach in medical and epidemiological research. This calculation was based on the estimated population of individuals with T1DM under 15 years of age (approximately 90,000 individuals). Considering the anticipated dropout rate and the expected effect size, the total sample size was calculated to be 372 participants. This estimate assumes a normal distribution of the population and that the outcomes of interest are representative of the general T1DM population in Spain. Assumptions made during the calculation include: A 95% confidence level and 5% margin of error; A normal distribution of the studied variables, consistent with similar research in the field.; A moderate effect size based on previous studies investigating similar interventions and a 20% dropout rate, which is typical for this type of intervention study.

Limitations of the sample size calculation include potential variability in the effect size, which could differ from our assumptions. Additionally, since participants are recruited through specific diabetes associations, this sample may not fully represent the broader T1DM population, potentially introducing selection bias. Given the potential variability in healthcare access, lifestyle factors, and diabetes management across different regions, participants’ region of origin was recorded to assess potential regional differences. This information allows us to explore whether geographical factors may influence the study outcomes and, if necessary, include region as a covariate in statistical analyses to control for potential biases due to regional heterogeneity.

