To assess **social skills** and **communication abilities** in adolescents, the latest validated version of the *Social Skills Questionnaire* (CHASO) by Caballo et al. [70] will be used. It comprises 40 Likert-type items (1–5) and evaluates 10 skills: *Interacting with Strangers*, *Expressing Positive Feelings*, *Facing Criticism*, *Interacting with People Who Attract Me*, *Staying Calm in the Face of Criticism*, *Public Speaking/Interacting with Superiors*, *Dealing with Embarrassment*, *Defending One’s Rights*, *Apologizing*, and *Rejecting Requests*. Psychometric properties show a reliability of α = 0.88 and a Guttman reliability coefficient of 0.86.

**Emotional awareness** will be evaluated using the ***Emotion Awareness Questionnaire*** (EAQ-30) by Rieffe et al. [71], adapted into Spanish by Samper-García et al. [72]. This 30-item Likert-type questionnaire (1–3) identifies how adolescents perceive their emotions, the intensity with which they feel them, and their ability to express them. It comprises six subscales: *Emotion Differentiation*, *Verbal Sharing*, *Not Hiding Emotions*, *Body Awareness*, *Emotion Analysis*, and *Attention to Others’ Emotions*. The validation of the scale in a Spanish sample yielded a reliability score of α = 0.74.

To evaluate **coping and problem-solving skills** in adolescents with T1DM, the short version of the ***Social Problem Solving Inventory – Revised*** (SPSI-R) by Zurilla and Nezu [73] will be used. This questionnaire measures cognitive, emotional, and behavioral responses to everyday problems or difficulties. It consists of 25 Likert-type items, grouped into five dimensions: *Rational Problem Solving* (RPS), *Avoidant Style* (AS), *Impulsive Style* (IS), *Positive Problem Orientation* (PPO), and *Negative Problem Orientation* (NPO). The questionnaire has demonstrated adequate psychometric properties [74], with reliability scores for the five dimensions as follows: RPS (α = 0.76), AS (α = 0.74), IS (α = 0.74), PPO (α = 0.67), and NPO (α = 0.76).

**Resilience** will be measured using the 10-item ***Connor-Davidson Resilience Scale*** (CD-RISC) [75], validated in Spanish by Notario-Pacheco et al. [76]. This scale uses Likert-type items (0–4) and has demonstrated strong psychometric properties (α = 0.85).

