Adolescent **self-concept** will be assessed using the latest version of the ***Garley Self-Concept Questionnaire*** (CAG) by García Torres [77]. This instrument aims to measure self-concept from a multidimensional perspective in adolescents. It consists of 48 Likert-type items, providing a global self-concept score, and is divided into six subdimensions: *Physical Self-Concept*, *Social Acceptance, Family Self-Concept*, *Intellectual Self-Concept*, *Self-Evaluation*, and *Sense of Control*. The questionnaire shows adequate psychometric properties for both the global score (α = 0.87) and the subscales.

Lastly, as a control variable, the ***Oviedo Infrequency Response Scale*** will be administered, developed by Fonseca-Pedrero et al. [78]. This scale consists of 12 Likert-type items (1–5) that are distributed throughout the questionnaire at key points. The items are organized into three groups of four, coded according to the questionnaire variable in which they are integrated. If a subject answers three or more items incorrectly, their questionnaire responses will be invalidated.

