Multiple hierarchical regression analyses will be conducted to examine the added predictive value of the experimental condition in explaining the intervention program’s efficacy. Hierarchical regression is a stepwise method where predictors are added to the model in blocks. The rationale behind the hierarchical approach is to assess the incremental contribution of each new block of predictors while controlling for the variables entered in the previous blocks. This allows for a clearer understanding of the unique variance explained by the experimental condition, after accounting for initial factors.

Step 1: The first block typically includes variables measured at time 1 that are believed to influence the dependent variable (i.e., the change between T2-T1 and T3-T1 for each variable). These could include baseline measures of emotional symptoms, quality of life, or disease-related factors.

Step 2: In subsequent blocks, new independent variables (predictors) are added. For example, in the second block, we would add the experimental condition (treatment vs. control) to assess its impact on the change in the dependent variable, controlling for the baseline scores. The dependent variable will be the change between pre- and post-intervention scores, as well as between pre-intervention and follow-up scores. A statistically significant change in the coefficient of determination in Model 2 (predictor: experimental condition, controlling for pre-intervention score) will be interpreted as added predictive value. A significant prediction from the experimental condition, controlling for pre-intervention score, will allow attribution of significant change to the intervention.

The Reliable Change Index (RCI) will be calculated for the scores of the evaluated variables. Reliable change will be determined by the extent to which an individual’s progress exceeds the natural fluctuation of measurements [80]. The RCI will be calculated using pre- and post-*emoTICare* means, along with the pre-intervention standard deviation and Cronbach’s alpha index.

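### The Reliable Change Index is defined for an individual's change but specified with pre and post means; read literally, it classifies no participant and does not test the group effect.

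*Protocol article*

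**What the plan says.** The RCI appears in the Data analysis section of the protocol article, after the hierarchical regressions. Its scope is general: "The Reliable Change Index (RCI) will be calculated for the scores of the evaluated variables". Its purpose is individual: "Reliable change will be determined by the extent to which an individual’s progress exceeds the natural fluctuation of measurements". The next sentence lists the ingredients: "The RCI will be calculated using pre- and post-*emoTICare* means, along with the pre-intervention standard deviation", to which it adds Cronbach's alpha.

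The section gives no denominator, no cut-off, no source for alpha (published or from the trial sample) and no plan to report how many participants change reliably. Earlier, the same section says that the main interest is the programme's overall effectiveness rather than conclusions about single participants.

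Two other places supply inputs. Sample size assumes "A moderate effect size based on previous studies investigating similar interventions and a 20% dropout rate", with no number for the effect. Psychological variables gives reliabilities for most instruments, for example "Psychometric properties show a reliability of α = 0.88" for the social skills questionnaire (CHASO) and "adequate psychometric properties for both the global score (α = 0.87) and the subscales" for the self-concept questionnaire (CAG).

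**The concern.** The two consecutive sentences do not fit together. A baseline SD combined with Cronbach's alpha gives the measurement error of one person's score. It is the right yardstick for asking whether that person's change is more than noise. It is the wrong yardstick for a mean over many people, whose error shrinks with sample size and depends on the spread of the change scores. A mean change divided by an individual error term therefore answers neither question.

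Two things are at stake. First, an ordinary average benefit could be labelled not reliable beside a clearly significant ANCOVA. Second, the RCI is the only individual-level analysis in the plan. If it is computed on means, adolescents who reliably deteriorated are averaged away.

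**Working it through.** **No figure to reproduce.** The article states no RCI value, formula or cut-off. The check asks what the named ingredients yield.

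**Assumptions, none stated in the article.** Denominator SD × sqrt(2(1 − alpha)), the usual standard error of a difference between two scores from one person; cut-off 1.96; within-group mean shift d = 0.5 baseline SD as a reading of a moderate effect.

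**Formulas.** With the mean change written as d × SD, RCI = d / sqrt(2(1 − alpha)). The shift needed to reach the cut-off is 1.96 × sqrt(2(1 − alpha)), in SD units.

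| Scale (alpha from Psychological variables) | alpha | RCI at 0.5 SD | Shift needed (SD) |
|---|---|---|---|
| CHASO | 0.88 | 1.02 | 0.96 |
| CAG global | 0.87 | 0.98 | 1.00 |
| CD-RISC | 0.85 | 0.91 | 1.07 |
| BIP-Q; SPSI-R RPS and NPO | 0.76 | 0.72 | 1.36 |
| EAQ-30; SPSI-R AS and IS | 0.74 | 0.69 | 1.41 |
| SDQ emotional symptoms | 0.71 | 0.66 | 1.49 |
| KIDSCREEN-27 (floor only) | 0.70 | 0.65 | 1.52 |
| SPSI-R PPO | 0.67 | 0.62 | 1.59 |
| SDQ behavioural problems | 0.58 | 0.55 | 1.80 |

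For CHASO: sqrt(2 × 0.12) = 0.490; 0.5 / 0.490 = 1.02; 1.96 × 0.490 = 0.96. For a 0.5 SD shift to reach 1.96, alpha would have to exceed 1 − (0.5/1.96)²/2 = 0.967.

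**Sensitivity.**
- At d = 0.8, the highest value is 0.8 / 0.490 = 1.63, still below 1.96.
- With a cut-off of 1.645, CHASO needs 0.81 SD.
- With the smaller denominator SD × sqrt(1 − alpha), CHASO needs 0.68 SD (cut-off 1.96) or 0.57 SD (cut-off 1.645).
- So 0.5 SD falls short under every variant. With that smaller denominator, a shift of about 0.7 to 0.8 SD could pass on the most reliable scales (CHASO, CAG global, CD-RISC).

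**The same shift against the error of a mean.** If 372 is the number before dropout, each arm keeps about 372/2 × 0.8 = 149. With pre-post correlation r (assumed 0.5 to 0.7), the SD of change is sqrt(2(1 − r)), that is 1.00 to 0.77 baseline SD. The z value for a within-arm shift of 0.5 SD is 0.5 × sqrt(149) / sqrt(2(1 − r)), about 6.1 to 7.9. The mean-based RCI for that shift is about 1 or less.

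**What a per-participant RCI would show.** Assume normal change scores and the same r. The share reliably improved is 1 − Φ((threshold − d) / sqrt(2(1 − r))).
- alpha 0.88: 28–32% with a 0.5 SD shift, 11–17% with none.
- alpha 0.76: 13–20% against 4–9%.
- alpha 0.70: 9–15% against 2.5–6%.

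At alpha 0.88 and a 0.5 SD average gain, the share reliably worse is Φ((−0.96 − 0.5) / sqrt(2(1 − r))): Φ(−1.46) = 7% at r = 0.5 and Φ(−1.88) = 3% at r = 0.7. A mean-based index cannot show these participants.

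**The case against.** The strongest defence is that the wording is merely loose. The preceding sentence speaks of an individual, the instruments are multi-item scales, and the section says that it works with composite item scores. The means could therefore be each participant's own mean item score before and after the programme. The cited RCI source, not available here, might settle it. This has force: the intent may well be individual. But the sentence does not say so, and an analyst who follows it literally computes the wrong quantity. Either way it needs rewording.

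It is also fair that the RCI is supplementary. No decision rule hangs on it, and effectiveness rests on MANCOVA/ANCOVA, Cohen's d and hierarchical regression.

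A reader might infer more than the document supports:
- **That every scale must fail.** Only scales with a stated alpha can be checked. KIDSCREEN-27 has only a floor, and the ECODI, SDQ Total Difficulties and the CAG subscales have no figure. Under the assumptions above, they would need an alpha above 0.967 to escape.
- **That only the game arm gets an RCI.** The phrase naming the programme may be just a time label. Elsewhere the section uses pre-intervention scores for both arms, and the RCI sentence restricts nothing by arm.
- **That the RCI would contradict a comparison with 99% power.** That figure is for a between-arm difference of 0.5 SD with 149 per arm. The RCI shift is within one arm, and the between-arm effect also depends on change in the controls.

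**Conclusion.** The point holds as an internal contradiction in a stated rule, not as missing detail: the index is defined for individuals and specified with means. Taken literally, the formula gives one uninterpretable number per scale. Under the standard denominator, a 1.96 cut-off and a 0.5 SD within-group shift, all assumed, that number is 0.55 to 1.02 where alpha is stated, and about 0.65 for KIDSCREEN-27 at its floor. The shift needed runs from 0.96 to 1.80 SD.

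The harm is confined to a supplementary result: a real average benefit could be described as not reliable, and reliable worsening would go unseen. Nothing here undermines the main ANCOVA or regression comparisons.

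**What to change.** Replace the sentence on RCI inputs. Compute for each participant, in both arms, (own post score − own T1 score) / [T1 SD × sqrt(2(1 − alpha))]. State the cut-off (for example ±1.96), the source of alpha for each scale, and which direction counts as improvement, since lower is better on some scales. Report the proportions reliably improved, unchanged and worsened by arm, with the between-arm difference and its 95% CI, as a supplementary descriptive result. Reporting both arms matters because some participants cross the threshold even with no mean shift.

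The cost is a reworded sentence and a short extra table. The regressions already use individual T2 − T1 and T3 − T1 changes, so no new data are needed. The article reports that neither recruitment nor data collection is complete, so the change can be made before analysis.
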